### Strategies to improve adherence to interventions {11c}

Participants can choose to fill in the pain diary and questionnaires electronically or on paper. Participants fill in every day the pain diary to score daily pain intensity on the NRS, number of daily cream applications and possibly used escape medication. Questionnaires are filled in only at the last day of each 14-day intervention period. When the pain diary is not filled in, the electronic questionnaire system Castor will send reminders the next day in the morning and the day after. Every 2 weeks the participant will visit the outpatient clinic to receive the study medication. The research physician checks at every visit the pain diary and questionnaires for completion.

In case the questionnaires are not filled in on the 14th day, the research physician will ask the participant to fill in the questionnaire at the visit on the 15th day.

When the pain diary is incomplete at the first visit, the research physician will stipulate the importance of filling in the pain diary and will monitor in Castor thereafter every day. In case the pain diary is not filled in, the patient will be phoned to ask the pain intensity on the NRS of the previous day, which will be noted, and will resolve the problem of poor adherence. When after the first 2 weeks less than 2 daily cream applications have been entered in the pain diary, the participant will be reinstructed during the second visit. The research physician will then monitor in Castor every day, and patients will be contacted in case of poor adherence. When poor adherence on paper diary and questionnaires is noticed in the first visit, daily phone calls will be performed in the second and third intervention periods. The outcomes will be registered in Castor and compared with the paper version. In case the participant experiences adverse events, one of the research physicians can be contacted for advice. Participants can contact the neurology department 24 h a day.

### Relevant concomitant care permitted or prohibited during the trial {11d}

Participants can continue their neuropathic pain medication when the dosage has been stable for at least one month. Acetaminophen and non-steroid anti-inflammatory drugs are allowed as escape medication for acute pain other than the neuropathic pain due to CIAP. Oral phenytoin, opiates and other topical analgesics are not allowed. Use of escape medication will be recorded in the on a daily base.

### Provisions for ancillary and post-trial care {30}

Participants can be reimbursed for transportation expenses. After the double-blind phase, participants can participate in a 1-year open-label extension phase. Hereafter, the general physician can prescribe phenytoin cream made by a compounding pharmacy. The UMCU has a liability insurance which is in accordance with article 7 of the Dutch law on medical research. This insurance provides cover for damage to research participants through injury or death caused by the trial. The insurance applies to the damage that becomes apparent during the trial or within 4 years after the end of the trial.

### Outcomes {12}

#### Primary outcome

The primary outcome is the mean difference between phenytoin 20% cream versus placebo cream in the 7-day average pain intensity, as measured by the NRS, over week 2 in DOBRET-positive participants.

#### Secondary outcomes

All secondary outcomes are evaluated for phenytoin 20% versus 10% versus placebo cream in DOBRET positive, negative and all participants.

The change between baseline and week 2 for each intervention is assessed for:Pain intensity measured on theNRSNeuropathic Pain Symptom Inventory (NPSI), evaluating on the NRS neuropathic pain characteristics [27]NRS for the 3 worst pain characteristics≥30% and ≥50% improvement on the NRS compared to placebo within one participant, reflecting at least moderate and at least substantial improvement [28]Patient-reported percentage of pain reduction at the end of the second week of each interventionOnset of the analgesic effect after applicationDuration of the analgesic effect after one applicationDaily number of cream applicationsUse of escape pain medicationQuality of life measured on thesubscales of the Brief Pain Inventory (sBPI), evaluating on the NRS pain interference regarding general activity, mood, walking ability, normal work, relations with other people, sleep, and enjoyment of life [29]EQ5-5D-5L, measuring the health status on the visual analogue scale, and on a 5-point scale pain/discomfort, anxiety/depression, mobility, self-care and usual activities [30]Patient Global Impression of Change Scale (PGIC), measured on a 7-point scale [31]To evaluate the safety and tolerability of phenytoin 10% and 20% creamTolerability is defined as time-to-discontinuation of an assigned treatment since randomization.Safety is based on the safety assessments including physical examinations, clinical laboratory evaluations, vital signs and frequency of AEs or SAEs. (S)AEs will be categorized according to the Common Terminology Criteria for Adverse Events and will be rated for severity and association with the study drug.Detection of phenytoin in plasmaPredictive value of DOBRET in sustained pain reduction due to phenytoin creamTo evaluate the correlation between the PCS and the pain-reducing effect of topical phenytoin

### Participant timeline {13}

Participant timeline is shown in Table 1.

**Table 1 Tab1:**
[figure not shown]
Time schedule of participant enrolment, allocation and assessments

*DOBRET* double-blind placebo-controlled response test, *EQ-5D-5L* euro quality of life questionnaire, *NPSI* neuropathic pain symptom inventory, *M* month, *NRS* 11-point numerical rating scale, *PCS* pain catastrophizing scale, *PGIC* patient global impression of change scale, *sBPI* subscales of brief pain inventory, *W* week

^a^The order of treatment will be randomized double-blindly

### Sample size {14}

We hypothesized a mean difference of 2 points on the NRS between placebo and the 20% cream (π1), and a mean difference of 1 point between 20% and 10% cream (π2). Based on preliminary data [21], we assumed for both treatment effects a standard deviation of 3.3 (standardized effect sizes: π1 = 0.61, π2 = 0.30). Using the same dataset, we conservatively assumed a correlation between NRS scores within participants (intraclass correlation) of 0.3. Seven participants per sequence (e.g. placebo–20%–10%, or 10%–placebo–20%) would be required to achieve 80% power and a two-sided significance level of 5% (= 7 × 6 sequences = 42 total sample size) [32]. Assuming a 10% drop-out rate, we will enrol 8 responding participants per group or 48 in total. DOBRET-negative participants are assumed to exhibit a mean difference of 1.5 point s (SD 4) on the NRS between placebo and the 20% cream, where 1 in 3 patients are assumed to be DOBRET-negative. This would result in a pooled overall treatment effect across DOBRET negative and positive participants of 1.83 (SD 4). Enrolling 24 DOBRET-negative and 48 DOBRET-positive participants would result in a power of 84% for the overall population.

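### One 80% power figure covers two hypothesised differences without naming a test; it does not hold for 20% versus 10% cream, which has about 38% power at 42 participants

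*Protocol article*

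**What the plan says.** All the figures are in Sample size {14} of the protocol article.

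- Two differences are hypothesised. The first: "We hypothesized a mean difference of 2 points on the NRS between placebo and the 20% cream (π1"). The second, for one active strength against the other, is 1 point (labelled π2).
- On variability: "we assumed for both treatment effects a standard deviation of 3.3 (standardized effect sizes: π1 = 0.61, π2 = 0.30"). On correlation: "we conservatively assumed a correlation between NRS scores within participants (intraclass correlation) of 0.3".
- Seven participants in each of six sequences, 42 in total, "would be required to achieve 80% power and a two-sided significance level of 5" per cent. With 10% drop-out this becomes 48 DOBRET-positive participants.
- For both strata together: "This would result in a pooled overall treatment effect across DOBRET negative and positive participants of 1.83 (SD 4"), from 1.5 points (SD 4) in DOBRET-negative participants, who are taken to be one in three. Then: "Enrolling 24 DOBRET-negative and 48 DOBRET-positive participants would result in a power of 84% for the overall population".

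Elsewhere, Outcomes {12} makes 20% cream versus placebo in DOBRET-positive participants the primary outcome. The Abstract lists 20% versus 10% among the key secondary outcomes. Statistical methods {20a} plans a likelihood ratio test of treatment, a factor with three levels.

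**The concern.** Two differences are set out side by side, each with its own standardised effect, and a single power follows. The text does not say whether that power belongs to 20% versus placebo, to "a mean difference of 1 point between 20% and 10% cream", or to a joint test of the three creams. The second effect is half the first at the same SD, so one sample size cannot give both the same power.

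The stake is how the dose comparison will be read. The Background says that no randomised trial has compared the two strengths. A non-significant 20%-versus-10% result could be taken as evidence of no dose difference, when the design would miss a true 1-point difference half the time or more.

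Two smaller matters sit in the same paragraph. Drop-out is applied to the 42 but not mentioned for the 84%, and the pooled SD is presented as a result although it does not follow from its components. The SD is also tied to treatment effects yet accompanied by an intraclass correlation, which is needed only if it is the SD of scores.

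**Working it through.** **Inputs** (Sample size {14}): differences 2 and 1; SD 3.3; ICC 0.3; two-sided 5%; n = 42; drop-out 10%; 48 + 24 = 72 enrolled; overall effect 1.83 with SD 4. The mean for 10% cream in the overall population is not given. I assume it lies midway, at 0.915; using 0.83 instead moves power by about 0.1 point.

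**1. Simple arithmetic.** 2/3.3 = 0.61 and 1/3.3 = 0.30. 42/0.9 = 46.7, so 48 in whole sequences. (2 × 2 + 1.5)/3 = 1.83. All agree with the plan.

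**2. Within-participant variability.** With 3.3 as the SD of scores, the SD of a paired difference is 3.3 × √(2 × 0.7) = 3.90, and the residual variance is 10.89 × 0.7 = 7.62. In the overall population, 4 × √1.4 = 4.73 and 16 × 0.7 = 11.2.

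**3. Which tests reproduce 80% and 84%?**

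- *Global test of three treatments* (2 df), noncentrality n × Σ(μ − mean)² / residual variance. DOBRET-positive means 0, 1, 2 give a sum of squares of 2. At n = 36 the noncentrality is 9.45 and power 77.2% (F) to 79.2% (chi-square). At n = 42 it is 11.02 and power 83.9-85.3%. So 42 is the first multiple of six above 80%. Overall, at n = 72, it is 72 × 1.674/11.2 = 10.76 and power 83.6-84.5%. Both figures fit.
- *20% versus placebo at α/2* (Bonferroni for two contrasts, t-test, range over the choice of degrees of freedom): 76.4-78.1% at 36, 83.5-84.7% at 42, 83.7-84.4% at 72. Both figures fit here too.
- *Two-sample formula ignoring the correlation:* 79.3% at 42 and 78.4% at 72. It fits the 80% only.
- *20% versus placebo, unadjusted:* about 91% at 42 and at 72. It fits neither figure.

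**4. Power of each contrast at n = 42.** Power = Φ(δ√n/SD of difference − 1.96).

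| SD of difference | 2 points (20% vs placebo) | 1 point (20% vs 10%) |
|---|---|---|
| 3.90 (3.3 is the SD of scores) | Φ(3.32 − 1.96) = 91.3%; paired t 90.0% | Φ(1.66 − 1.96) = 38.2%; paired t 36.7% |
| 3.30 (3.3 is the SD of the difference) | Φ(3.93 − 1.96) = 97.5% | Φ(1.964 − 1.960) = 50.2% |

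For 80% power to detect 1 point, n = (1.96 + 0.842)² × SD² = 7.85 × 15.25 = 120 on the first reading, and 7.85 × 10.89 = 86 on the second. With all 48 DOBRET-positive participants retained, power for 1 point is still only 42.6% or 55.5%.

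**5. Drop-out in the overall population.** 72 × 0.9 = 64.8, or 65. Applying the plan's own ratio of 42 completers to 48 enrolled gives 42 + 21 = 63. With SD 4 and 63-65 completers, the global test has 78.0-80.4% and 20% versus placebo 85.6-87.6%.

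**6. Pooled SD.** Mixing SD 3.3 and SD 4 at 2:1, with means 2 and 1.5: √(⅔ × 10.89 + ⅓ × 16 + 2/9 × 0.25) = √12.65 = 3.56, not 4. With 3.56 and 63-65 completers, the global F test has about 87-88% and 20% versus placebo about 92-94%.

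**The case against.** The strongest reply is that nothing important is wrong. The primary contrast exceeds 80%, and sizing in multiples of six naturally overshoots. If a global test was used, it matches the likelihood ratio test of the three-level treatment factor in Statistical methods {20a}. On that view the 1-point difference is only an input to a three-mean calculation. The section never says in so many words that 20% versus 10% is powered, and low power for a secondary contrast is not in itself an error. All of this stands, and it limits the point to what the section states and leaves open.

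Some stronger readings do not follow from the document:

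- *The figures come only from a global three-arm test.* Step 3 shows that a two-contrast Bonferroni test fits both equally well. The cited method source is not available, so the formula cannot be confirmed.
- *The 84% was certainly computed without drop-out.* The wording refers to those enrolled, and the two tests that fit both figures need all 72, so this is likely. It is not proven: an unadjusted paired t-test on 63 completers gives 85.6%, within two points of 84%.
- *The overall analysis falls short.* Removing 10% entirely is a worst case, because the mixed model uses completed periods. SD 4 is also conservative: with 3.56 and 10% loss, power is above 84% on either test.

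What the reply does not answer is that no candidate test brings 20% versus 10% near 80%. That several tests fit is itself the sign that the section does not say what was powered.

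**Conclusion.** The point holds as a defect in the stated power, not in the sample size. The 80% is unattached to any test or contrast, and it does not hold for the second hypothesised difference. At 42 participants, 20% versus 10% has about 37-38% power if 3.3 is the SD of scores (the reading that the correlation implies) and 50% if it is the SD of the difference. The matching figures for the primary contrast are 90-91% and 97.5%. A reader might infer that the trial is underpowered for its primary outcome; the plan's own inputs show the opposite.

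The 84% corresponds to 72 participants without loss under the global or Bonferroni test. It becomes about 78-80% with SD 4 and 10% drop-out, if drop-outs contribute nothing. The pooled SD of 4 is on the safe side but is mislabelled as a result of the mix.

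These figures rest on the plan's effects, SDs and correlation, on an assumed midway mean for 10% cream in the overall population, and on simple paired or 2-df tests standing in for the mixed model.

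**What to change.** Keep the sample size and revise the text of Sample size {14}:

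- Name the test and contrast behind the 80% and behind the 84%.
- Say whether 3.3 is the SD of scores or of within-participant differences.
- State that 42 evaluable participants give about 90-91% power for 20% versus placebo and about 38% for 20% versus 10% (97.5% and 50% on the other SD reading). Say that the dose comparison is therefore for estimation with a confidence interval, and that a null result is not evidence of no dose difference.
- Restate overall-population power after 10% drop-out for the named test, and deal with the pooled SD at the same time. Either label SD 4 as a deliberate conservative choice (63-65 completers: about 78-80% global, 86-88% for 20% versus placebo), or use 3.56 (about 87-88% and 92-94%).

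The cost is a few sentences and one less favourable figure for the dose comparison. No participants, visits or analyses are added.

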### Recruitment {15}

On behalf of treating physicians, a standardized letter will be sent to patients who visited the neurology outpatient clinic of the UMCU from 2016 onwards and who were diagnosed with CIAP. When patients are interested to participate, they can contact the research physician, who will recruit the patients. The patients will be fully informed about the study, verbally and in writing, with special emphasis pertaining to the explanation of blood withdrawal for study purposes. The patients will be given at least one week to decide about their participation. Also, letters are sent to neurology departments of surrounding hospitals asking colleagues to refer eligible patients. On several websites such as the Princess Beatrix Muscle Foundation, the trial is described and interested patients can contact the outpatient clinic.

## Assignment of interventions: allocation

### Sequence generation {16a}

The pharmacist who prepares the study medication externally, according to Good Manufacturing Practice (GMP pharmacist) will randomly assign a label A, B or C to the tubes each containing 90 g of phenytoin 10%, 20% or placebo cream. For the DOBRET the GMP pharmacist will randomly assign a label A or B to the test tubes with phenytoin 10% cream and placebo cream. The final labelling on each study medication set of tubes will thus be S1A, S1B and S1C (first box), S2A, S2B and S2C (second box), and so on. The final labelling on each DOBRET tube set will thus be D1A and D1B (first box), D2A and D2B (second box), and so on. The study medication and DOBRET randomization list will be given by the GMP pharmacist to the UMCU pharmacist and only accessible by the UMCU pharmacist.

### Concealment mechanism {16b}

A blinded research physician will perform DOBRET, were after the results will be sent to the UMCU pharmacist, who will stratify participants according to the result of the DOBRET: 48 participants into the DOBRET positive arm, and 24 participants into the DOBRET negative arm. The tubes and cream are identical in appearance, to ensure the blinding of the participants and the treating physicians.

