## Statistical methods

### Statistical methods for primary and secondary outcomes {20a}

Descriptive statistics will be used for baseline characteristics/demographics (age, sex, highest degree of education, country of birth, profession, duration and localization of pain, current neuropathic pain therapy, and past analgesic use), use of study creams (daily amount of use, number of daily applications, onset, duration and percentage of analgesic effect).

The primary endpoint measured on the NRS, as well as all other secondary endpoints, will be analysed according to the intention-to-treat (ITT) principle, incorporating all participants randomized irrespective of receiving treatment and having at least one efficacy measurement. For the primary analysis, the treatment effect will be determined in participants with a DOBRET-positive response at screening, evaluating the mean difference in NRS at week 2 between placebo and phenytoin 20% cream. Linear mixed-effects models (LME) will be used to account for the intra-individual clustering of observations. In brief, we will use an LME with fixed effects for time (week 1 or 2), treatment period (1 or 2 or 3), treatment (20% or 10% or placebo), the interaction between time and treatment, and NRS score at screening. The random part will be modelled with a random intercept and slope for time per individual, and an unstructured covariance matrix. The random slope for time will be kept in the model only if statistically significant. The likelihood ratio test will be used to test the significance of treatment; 95% confidence intervals will be based on the profile likelihood. Sensitivity analyses will be performed to evaluate (1) treatment-period interaction to assess potential carry-over effects and (2) per-protocol analysis involving all participants who completed the study. As secondary analysis, we will evaluate the treatment effect in all randomized patients irrespective of DOBRET, and explore the interaction between DOBRET outcome and treatment using additional interaction terms. Treatment effects on the NPSI, EQ-5D-5L, sBPI and PGIC will be evaluated in the same manner as the primary outcome.

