### Methods for additional analyses (e.g. subgroup analyses) {20b}

As an exploratory objective, we will determine the test accuracy for DOBRET to identify participants who benefited from treatment, where treatment benefit is defined as a 30% reduction from baseline NRS. The following factors will be tested in the models for confounding effects: pain duration, and intensity, use of co-medication and escape medication, pain characteristics, pain catastrophizing score, level of education and duration of effect of study medication. Linear regression analyses will be used to evaluate the correlation of pain reduction with pain duration, and intensity, use of co-medication and escape medication, pain characteristics, catastrophizing, level of education and duration of effect. For all analyses, results will be considered significant when *p* < 0.05. For the subgroup analysis, we will correct the *p*-value according to Bonferroni.

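### If DOBRET's test accuracy is reported as unweighted sensitivity and specificity, the values depend on the 48:24 enrolment quota

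*Protocol article*

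**What the plan says.** Under Concealment mechanism {16b}, the pharmacist stratifies by DOBRET result: "48 participants into the DOBRET positive arm, and 24 participants into the DOBRET negative arm". Trial design {8} and Sample size {14} give the same numbers. Under Implementation {16c}, participants are enrolled after the test has been done.

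Methods for additional analyses {20b} sets an exploratory objective: "we will determine the test accuracy for DOBRET to identify participants who benefited from treatment". It names no accuracy measure. The yardstick for benefit is an NRS score 30% below its baseline value. Predictive value is a separate item in the list of secondary outcomes. Trial design {8} adds that the trial will explore which responder definition for DOBRET predicts sustained relief.

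The only stated link between the quota and the patients tested is an assumption in Sample size {14}, for which the article gives no source: "where 1 in 3 patients are assumed to be DOBRET-negative". The analysis of everyone together is defined on randomised participants: "we will evaluate the treatment effect in all randomized patients irrespective of DOBRET".

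**The concern.** The sample is drawn on the test result in a ratio chosen by the investigators. Such sampling leaves the proportion who benefit among positives, and among negatives, estimable. Sensitivity and specificity condition the other way, on benefit. They therefore combine the two strata in proportions that the quota sets, not the patients who came for testing.

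If fewer than two thirds of tested patients are positive, unweighted sensitivity is too high and specificity too low. If more are positive, the reverse holds. Whether DOBRET can identify responders is the main secondary objective, so an accuracy figure that moves with the enrolment ratio could mislead readers about the test.

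**Working it through.** **Inputs.** From the article: 48 positive and 24 negative participants; assumed negative share 1 in 3; 20% cream versus placebo effect of 2 points in positives ("We hypothesized a mean difference of 2 points on the NRS between placebo and the 20% cream") and 1.5 points in negatives. Not in the documents, and assumed here: benefit rate a in positives and b in negatives.

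**The plan's own figures.** Pooled effect = (48 × 2 + 24 × 1.5)/72 = 132/72 = 1.83, as stated. The stated 84% power for the overall population is also reproduced. A 2-df F test of three treatments in a cross-over (n = 72, SD 4, within-participant correlation 0.3, 10% cream midway) gives 83.6%. The quota share 24/72 equals the assumed 1 in 3, so quota and assumed mix agree.

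**Accuracy as a function of the share of positives p.**

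- Sensitivity = pa / [pa + (1 − p)b]
- Specificity = (1 − p)(1 − b) / [(1 − p)(1 − b) + p(1 − a)]

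With a = 0.60 and b = 0.35, the quota sample is expected to contain 48 × 0.60 = 28.8 positives and 24 × 0.35 = 8.4 negatives who benefit. Sensitivity is 28.8/37.2 = 77%. Among those who do not benefit there are 24 × 0.65 = 15.6 negatives and 48 × 0.40 = 19.2 positives, so specificity is 15.6/34.8 = 45%.

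At p = 0.50, sensitivity is 0.300/(0.300 + 0.175) = 63% and specificity is 0.325/(0.325 + 0.200) = 62%.

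Sensitivity/specificity (%) for several assumed pairs of benefit rates (positives/negatives):

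| Share positive | 60/35 | 60/30 | 50/35 | 70/20 |
|---|---|---|---|---|
| 40% | 53/71 | 57/72 | 49/66 | 70/80 |
| 50% | 63/62 | 67/64 | 59/57 | 78/73 |
| 66.7% (quota) | 77/45 | 80/47 | 74/39 | 88/57 |
| 80% | 87/29 | 89/30 | 85/25 | 93/40 |

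The pattern does not hinge on one pair of rates. An uninformative test (a = b) would show sensitivity 48/72 = 67% and specificity 24/72 = 33% from the quota alone.

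**What does not move.** The positive predictive value is a, estimated in the 48. The negative predictive value is 1 − b, estimated in the 24. Neither contains p. Stratum effects and the DOBRET-by-treatment interaction do not contain p either.

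**Pooled effect.** Under the article's own stratum effects it is 2p + 1.5(1 − p): 1.70 at 40%, 1.75 at 50% and 1.90 at 80%, against 1.83. The largest shift in that range is 1.83 − 1.70 = 0.13 NRS points.

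**Alternative cut-offs.** Moving the cut-off transfers participants from one original stratum into the other group. At least one of the new groups then mixes both strata, and its predictive value also depends on 48:24.

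**The case against.** The strongest case against the point is that the article names neither sensitivity nor specificity. Where it names a measure, it speaks of predictive value, which the quota leaves alone. The accuracy analysis is exploratory. The quota was matched to the expected mix, so there is no distortion if that expectation is right, and little if it is nearly right: at a 70% share with the 60/35 rates, the figures are 80% and 41%, against 77% and 45%. Weights for an exploratory analysis commonly belong in the full protocol or the analysis plan, which are not shown. The pharmacist receives the DOBRET results, so the counts may already exist.

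Most of this stands and limits the point. Two parts do not dispose of it. Test accuracy for identifying those who benefited ordinarily means sensitivity and specificity, and predictive value is listed separately. A later analysis plan can apply weights only if the results of patients tested but not enrolled were kept, and that is decided during conduct.

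A reader might go further and infer that the effect in all participants is biased as well, since secondary outcomes cover "placebo cream in DOBRET positive, negative and all participants". The documents do not support that. The analysis is defined on those randomised, the article does not present it as the effect in all patients tested, and the shift is small. A reader might also infer that the accuracy figures are certain to be wrong. That would require evidence that the share of positives differs from two thirds, and the article gives none.

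**Conclusion.** The point holds as a conditional one. Unweighted sensitivity and specificity from this sample describe the tested patients only if close to two thirds of them are DOBRET-positive, an assumption that the stated analyses do not check. In the 60/35 illustration, a true share of 50% means sensitivity is overstated by 14 percentage points (77 against 63) and specificity understated by 17 (45 against 62). At 80% the errors reverse: 10 points too low and 16 too high. These sizes rest on assumed benefit rates and shares. The direction follows from the design whenever negatives as well as positives include some who benefit and some who do not.

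The primary analysis is restricted to DOBRET-positive participants and is untouched. This is a risk to an exploratory analysis that serves the main secondary objective. It is worth correcting because the correction is cheap.

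**What to change.** Keep the DOBRET result of every patient tested, including those tested after a stratum is full, and report the observed share of positives. Weight sensitivity and specificity to that share, and do the same for results under alternative responder cut-offs. If the share cannot be established, report only the stratum-specific predictive values for the original definition.

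The cost is a screening count, one weight per stratum and wider intervals. The intervals should carry the uncertainty in the observed share, and unequal weighting loses precision as that share moves away from two thirds. For a simple weighted mean over the strata, the effective sample size is 1/[p²/48 + (1 − p)²/24]: 72 at two thirds, 64 at 50%, 54.5 at 40% and 66.7 at 80%. For sensitivity and specificity the widening also depends on the benefit rates and on the number tested, which the article does not give.
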